### *Outcomes*

The primary endpoint is the rate of HA bloodstream infections with Gram-negative pathogens in all preterm and newborn infants who received colonization screening. This outcome is defined clinically according to NEO-KISS criteria (at least two clinical signs of sepsis + one laboratory sign, e.g. increase in C-reactive protein > 10mg/l) after 72 hours of life and requires the detection of a Gram-negative pathogen in the blood culture. Blood-culture isolates will be sent from the study centers to the study management.

Key secondary endpoint is the 2MRGN transmission rate which is assumed if another infant is colonized with the same 2MRGN pathogen after 2MRGN colonization or infection of an infant

requiring intensive care in a temporal (maximum 90 days) and spatial context (potential contact in the intensive care unit) (26). This assumption is made if, in addition to pathogen identification, the antimicrobial susceptibility testing patterns are identical. Suspected transmission of or bloodstream infection with an 2MRGN pathogen will be reported to the study management as severe adverse event within 24 hours.

Transmission/outbreak management remains the responsibility of the local interdisciplinary infection control team and is carried out according to local standards, including the decision whether to initiate genetic identity testing in the acute situation. 2MRGN isolates will be shipped from local sites and molecular typing will be performed at the Department of Infectious Diseases and Medical Microbiology at the University of Lübeck. Other secondary outcomes at the level of study sites per period ("study phase") are:

- Rate of clinical and culture proven infections
- Rate of infection outbreaks
- Number of initiated antibiotic cycles
- Duration of antibiotic treatment (days)
- Exposure to reserve antibiotics, including Carbapenems per study site in % infants.

To assure documentation of relevant outcomes, intensive interdisciplinary collaboration (neonatology/infectiology/hygiene/pharmacy/management) is required. Data are collected by monthly cluster report forms on infection and transmission rates and yearly surveillance of antibiotic use, disinfectant consumption, and cost estimations.

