To allow for patient-level description, the data set is re-structured to contain one line per patient based on the documented number of patients admitted to the site [Aufnahmen\_Neo]. In this, the following month-level variables are used to construct the following patient-level variables indicating presence or absence of the event:

| Variable                                     | Month-level
(original variable) | Patient-level
(constructed variable) |
|----------------------------------------------|------------------------------------|-----------------------------------------|
| Gram negative infection                      | Anzahl_gramNeg_nurLOS              | gramNeg_nurLOS                          |
| At least one suspected transmission          | Transm_Patient                     | Transm                                  |
| At least one suspected transmission of 2MRGN | Transmission_2MRGN_Patient_SAE     | Transm2m                                |
| Clinical infection                           | Anzahl_kl_Sepsis_allg              | Sepsis                                  |
| Any BSI                                      | Anzahl_BKpos_Sepsis_allg           | Sepsis_pos                              |
| 2MRGN BSI                                    | Anzahl_2MRGN_LOS                   | LOS                                     |

For the estimation of the GEE models, a cluster variable [Cluster] is created that combines the information from the site identifier [Klinik\_ID] with the variable indicating the phase [Randomisierung], so that every site corresponds to two clusters, one for every phase.

The variable counting the number started reserve antibiotics in a month [Anzahl\_beg\_Reserve\_ATB] is dichotomized to indicate whether at least one treatment with a reserve antibiotic was started or not [Beg\_Reserve\_ATB].

In addition, the clinical project management team surveys the participating sites about consumption of disinfectant and estimated costs. This data will separately be transferred to the IMBS for analysis.

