### 9.4.2 Efficacy Outcome Variables on the level of patients

For the following binary variables, the count of patients without the event is reconstructed:

- Transmission of 2MRGN [Anzahl\_gramNeg\_nurLOS\_negativ]
- Any transmission [Transm\_Patient\_negativ]
- Any BSI [Anzahl\_BKpos\_Sepsis\_allg\_negativ]
- 2MRGN BSI [Transmission\_2MRGN\_Patient\_SAE\_negativ]
- Clinical infection [Anzahl\_kl\_Sepsis\_allg\_negativ]

For these, the below analyses are performed:

|                  |                                                                                                                                                                                                                                                                                        |
|------------------|----------------------------------------------------------------------------------------------------------------------------------------------------------------------------------------------------------------------------------------------------------------------------------------|
| Outcome variable | Anzahl_gramNeg_nurLOS, Anzahl_gramNeg_nurLOS_negativ, Transm_Patient, Transm_Patient_negativ, Anzahl_BKpos_Sepsis_allg, Anzahl_BKpos_Sepsis_allg_negativ, Transmission_2MRGN_Patient_SAE, Transmission_2MRGN_Patient_SAE_negativ, Anzahl_kl_Sepsis_allg, Anzahl_kl_Sepsis_allg_negativ |
| Endpoint         | Transmission of 2MRGN, any transmission, any BSI, 2MRGN BSI, clinical infection                                                                                                                                                                                                        |
| Effect measure   | Risk difference                                                                                                                                                                                                                                                                        |

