| Adjustments for covariates | None                                                                                                                                                                                                                                                                                                                                                                                                                                                                                                                                                                                                                                                                                                                                                                                                                                                                                                                                                                                                                                                                                                                               |
| Main estimator             | 
Risk differences are estimated from a GEE logistic regression model with identity link using the following command from the R-library <code>geepack</code>:
 <pre>geeglm(cbind(events, nonevents) ~ Randomisierung, family = binomial(link = "identity"), id = Cluster, corstr = "independence")</pre> 
with the variable <code>Randomisierung</code> indicating the phase (CO vs. IV) and <code>events</code> and <code>nonevents</code> being one of the five variable pairs
 
 
• <code>Anzahl_gramNeg_nurLOS</code>, <code>Anzahl_gramNeg_nurLOS_negativ</code>
 
• <code>Transm_Patient</code>, <code>Transm_Patient_negativ</code>
 
• <code>Anzahl_BKpos_Sepsis_allg</code>, <code>Anzahl_BKpos_Sepsis_allg_negativ</code>
 
• <code>Transmission_2MRGN_Patient_SAE</code>, <code>Transmission_2MRGN_Patient_SAE_negativ</code>
 
• <code>Anzahl_kl_Sepsis_allg</code>, <code>Anzahl_kl_Sepsis_allg_negativ</code>
 
 
The risk difference with regard to the intervention is estimated accordingly with 95% confidence intervals.
 |

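### SAP section 9.4.2 attaches the wrong variables to patient-level 2MRGN transmission and 2MRGN BSI, and the true 2MRGN BSI variable enters no specified model

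*Combined protocol and SAP*

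**What the plan says.** SAP section 5 (Database) is the data dictionary. Its table of month-level and patient-level variables contains these three rows:

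- "Gram negative infection | Anzahl_gramNeg_nurLOS"
- "At least one suspected transmission of 2MRGN | Transmission_2MRGN_Patient_SAE"
- "2MRGN BSI | Anzahl_2MRGN_LOS"

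Section 9.3 follows the dictionary: the primary analysis of Gram-negative BSI uses `Anzahl_gramNeg_nurLOS` and its `_negativ` count.

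The bullet list in section 9.4.2 does not. It gives "Transmission of 2MRGN [Anzahl\_gramNeg\_nurLOS\_negativ" and, three bullets later, "2MRGN BSI [Transmission\_2MRGN\_Patient\_SAE\_negativ". The outcome-variable row and the endpoint row of the 9.4.2 table keep the order of the bullets. The main-estimator row then supplies the model inputs, with events and non-events "being one of the five variable pairs"; these are the same five pairs in the same order.

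The protocol's Outcomes section states: "Key secondary endpoint is the 2MRGN transmission rate". SAP section 4.1 lists both 2MRGN transmission and 2MRGN BSI as patient-level secondary endpoints.

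**The concern.** Sections 5 and 9.4.2 give different meanings to the same variable names, and both cannot be right. A variable whose name begins with `Transmission_2MRGN` is labelled as a bloodstream infection, and the primary-endpoint variable is labelled as a transmission.

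The study arms differ only in the care of 2MRGN-colonised infants, so 2MRGN transmission and 2MRGN BSI are arguably the outcomes nearest to what is being changed. The protocol also treats both as events to be reported to the study management as severe adverse events within 24 hours, and SAP section 9.4.3 says that no further safety variables were assessed. If 9.4.2 is programmed as written, the report would present one endpoint's data under another's name for both outcomes.

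**Working it through.** The plan gives no figure to reproduce here. The check sets each endpoint in 9.4.2 beside the section 5 definition of the variable attached to it.

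| Endpoint in 9.4.2 | Variable attached in 9.4.2 | Meaning of that variable in section 5 | Agree? |
|---|---|---|---|
| Transmission of 2MRGN | `Anzahl_gramNeg_nurLOS` | Gram-negative infection | No |
| Any transmission | `Transm_Patient` | Suspected transmission | Yes |
| Any BSI | `Anzahl_BKpos_Sepsis_allg` | Any BSI | Yes |
| 2MRGN BSI | `Transmission_2MRGN_Patient_SAE` | Suspected 2MRGN transmission | No |
| Clinical infection | `Anzahl_kl_Sepsis_allg` | Clinical infection | Yes |

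Three of five agree and two do not.

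**Which section is right.** Section 9.3 uses `Anzahl_gramNeg_nurLOS` for Gram-negative BSI, as section 5 does, and the names themselves fit section 5. The error is therefore in 9.4.2.

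**Coverage.** Section 5 defines six event variables. The five pairs in 9.4.2 use five of them, and one of those five is the primary variable already used in 9.3. The sixth, "Anzahl_2MRGN_LOS", appears only in section 5 and in the plausibility rule of section 8.2. No model in 9.3, 9.4.1 or 9.4.2 uses it, so 6 − 5 = 1 event variable has no specified model, and it is the one for an endpoint listed in section 4.1.

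**What the first pair would return.** The calls in 9.3 and 9.4.2 compare as follows.

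| Element | Primary (9.3) | Transmission of 2MRGN as written (9.4.2) |
|---|---|---|
| Outcome pair | `Anzahl_gramNeg_nurLOS`, `Anzahl_gramNeg_nurLOS_negativ` | the same |
| Predictor | `Randomisierung` | the same |
| Family and link | binomial, identity | the same |
| Cluster id | `Cluster` | the same |
| Working correlation | independence | the same |

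With every element equal, the fitted risk difference and its 95% confidence interval are those of the primary analysis.

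**What the fourth pair would return.** It gives a valid risk difference for suspected 2MRGN transmission, printed under the heading of 2MRGN BSI.

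**The case against.** The strongest reply is that this is a drafting slip with an obvious intended meaning and limited reach. Several parts of that reply stand:

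- The primary estimand, model and test are untouched.
- Every analysis in 9.4.2 is declared descriptive and has no hypothesis, so no error rate or power changes.
- Month-level 2MRGN transmission is labelled and modelled correctly in 9.4.1, and the patient-level transmission data would still be fitted, though under the wrong label.
- Section 5 constructs a patient-level 2MRGN BSI variable, `LOS`, for description, so a simple count remains possible. The exact statement is that no specified model uses the 2MRGN BSI data.
- Only the bullet list ties names to endpoints explicitly. The outcome and endpoint rows do so by position, and the estimator list carries no endpoint labels. Read as a set, the estimator list has one wrong entry: the primary pair stands where the 2MRGN BSI pair should be.
- An analyst may well notice. The names describe themselves, and a secondary result identical to the primary would be conspicuous. The documents do not show the code.

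These points limit the consequences but do not remove the error. The shared order makes the positional reading the natural one, so all three statements in 9.4.2 point the same way. Even on the most generous reading, the model list still omits 2MRGN BSI. Section 9.1 plans no blinded data review that might catch the mismatch, and a silent correction by the analyst would be an undocumented departure from the SAP.

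**Conclusion.** The specification in 9.4.2 is wrong as written. Two of five patient-level secondary endpoints carry another endpoint's data, one of them being the protocol's key secondary. One of the six event variables, that for 2MRGN BSI, has no model, and the primary result would appear a second time under another name. The damage is confined to descriptive patient-level secondary analyses. The stated consequences assume that the code follows 9.4.2 literally; the contradiction between sections 5 and 9.4.2 depends on no assumption. It should be corrected before analysis.

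**What to change.** Apply the section 5 mapping in all three places in 9.4.2:

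1. **Bullet list:** Transmission of 2MRGN takes `Transmission_2MRGN_Patient_SAE_negativ`; 2MRGN BSI takes `Anzahl_2MRGN_LOS_negativ`.
2. **Outcome-variable row:** put `Transmission_2MRGN_Patient_SAE` and its `_negativ` count first and `Anzahl_2MRGN_LOS` and its `_negativ` count fourth, so that the order again matches the endpoint row.
3. **Estimator list:** make the same change and write the endpoint beside each pair.

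Remove `Anzahl_gramNeg_nurLOS` and its `_negativ` count from 9.4.2, since 9.3 covers them. The other three pairs stay, and all five then agree with section 5. Record the change as a dated SAP correction and check any existing code against it. If results have already been produced from 9.4.2, rerun the two affected rows and say so in the report. No new data and no design change are needed.

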#### *The rationale for a cluster-randomized controlled non-inferiority study*

The clinical equipoise for this randomized controlled trial (RCT) is based on a potential benefit of extended barrier precautions for reducing HA infection risk and outbreaks in vulnerable babies versus negative effects of potentially non-effective extended hygiene measures. Specifically, a retrospective cohort study including 337 infants suggested that the combined

use of alcohol-based hand rub and gloves leads to a 2.8 fold reduction of HA infections (9). Using a hand hygiene protocol with hand washing, hand rub and gloves a single center study including 200 preterm infants born at 32-36 weeks of gestation reduced HA infections from five to zero cases over a 14-month observation period (10). In a prospective trial including 120 preterm infants, Kaufman (11) noted a 17% reduction of Gram-positive infections and 64% fewer central line-associated bloodstream infections when non-sterile gloves were used as compared to hand disinfection alone. One of the largest efforts in adults, the Benefits of Universal Glove and Gown (BUGG) cluster randomized trial, found non significant effect of universal glove use on preventing infections with MDRO (12). Hence there is a need to evaluate the potential benefits of extended precautions and balance against negative effects. Since the introduction of routine colonization screening in 2013, observational data from German NICUs revealed no significant changes in infection rates and sepsis mortality caused by pathogens included in the screening (3, 13). While the rate of culture-proven sepsis with Gram-positive bacteria had already been declining in centers participating in a large German cohort study (German neonatal network, GNN) before the screening guideline, the infection rates with Gram-negative pathogens and MRGN remained constant, i.a. 2.5-3%, and < 0.5%, respectively (3). These data provide the key argument for the non-inferiority design of the our trial.

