#### *Sample size calculation and statistical analysis*

GNN and PRIMAL centers treat on average 150 preterm and critically ill neonates per year with compulsory colonization screening. The center-specific rates of Gram-negative HA infection ranges between 1.5 and 6%. Based on single center data as described above and other cohort studies (20-22) we expect 10% of these infants to be colonized with 2MRGN during hospital stay, i.e. 180 infants per 12 months observational period.

Based on previous data, we assume an intracluster correlation of maximally 0.01. Given that the observed correlation is very low, the time lag between the two trial periods is long and different patients are included in the two trial periods at each site. No carry-over effects are assumed, as we are not expecting that effects of one treatment period would influence the second period (after cross-over) since medical care-givers are aware of the study period they are in. Data from two periods at one site are regarded as two independent sites. We further assume a frequency of Gram-negative HA infections in the controls of 3% and a non-inferiority limit of 5%. Striving for a power of 0.8 ( $1-\beta$ ) with a one-sided significance level  $\alpha$  of 0.05, at least  $n=18$  patients per site and phase are required for analysis with 12 sites, thus  $n=432$  in total. To allow for a maximal drop-out of 10% drop-out, at least 480 patients need to be included.

The primary data analysis will be performed according to the intention-to-treat principle (non-linear mixed effect regression models, logit link). Generalized estimating equations are performed to determine the infection rates between the two regimens. Secondary endpoints are analysed as the primary endpoint per individual or per cluster.

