## 5 Database

The database is the data taken over from the clinical project management team according to Chapter 3. In this, data is documented entirely on an aggregated level, i.e., per month per site.

The data is structured as follows:

- Every of the 12 sites participates in the study in two phases, in one of which hand disinfection alone (IV), in the other hand disinfection plus gloves and gowns is applied (CO). The order of the two phases is randomized.
- Every phase has a duration of 12 months, so that for every site, data is collected for 24 months.
- Each of the two phases at one site is considered one cluster.
- Given the aggregation of the data in months, the observational unit is the month (month-level variables).
- Some variables give the count of patients with a specific event. From this and the number of admissions in that month, the number of patients without the specific events is constructed as well as data on patient-level is constructed for analyses (patient-level variables).

To obtain the count of patients without a specific event, the number of events is subtracted from the number of admissions [Aufnahmen\_Neo] rendering the following additional variables:

| Count of patients with the event
(original variable) | Count of patients without the event
(constructed variable) |
|---------------------------------------------------------|---------------------------------------------------------------|
| Anzahl_gramNeg_nurLOS                                   | Anzahl_gramNeg_nurLOS_negativ                                 |
| Transm_Patient                                          | Transm_Patient_negativ                                        |
| Transmission_2MRGN_Patient_SAE                          | Transmission_2MRGN_Patient_SAE_negativ                        |
| Anzahl_kl_Sepsis_allg                                   | Anzahl_kl_Sepsis_allg_negativ                                 |
| Anzahl_BKpos_Sepsis_allg                                | Anzahl_BKpos_Sepsis_allg_negativ                              |
| Anzahl_2MRGN_LOS                                        | Anzahl_2MRGN_LOS_negativ                                      |

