| Hypothesis                 | n.a.                                                                                                                                                                                                                                                                                                                                                                                                                                                                                                                                                                                                                                                                                                                                                                                                                                                                                                                                                                                                                                                                                                                               |
| Significance level         | Descriptive analysis only                                                                                                                                                                                                                                                                                                                                                                                                                                                                                                                                                                                                                                                                                                                                                                                                                                                                                                                                                                                                                                                                                                          |

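### If one regimen has no events for a rare patient-level secondary endpoint such as 2MRGN BSI, the identity-link GEE in SAP 9.4.2 either fails to fit or gives that regimen zero variance, and no fallback is named

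*Combined protocol and SAP*

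**What the plan says.** SAP 9.4.2 lists the patient-level secondary endpoints as "Transmission of 2MRGN, any transmission, any BSI, 2MRGN BSI, clinical infection". For all of them the main estimator is the same: "Risk differences are estimated from a GEE logistic regression model with identity link", by one unadjusted `geeglm` command with binomial family and independence working correlation. On output it says only: "The risk difference with regard to the intervention is estimated accordingly with 95% confidence intervals". The section sets no hypothesis, and the significance level reads "Descriptive analysis only".

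On the data, SAP section 5 says "Every of the 12 sites participates in the study in two phases" and defines the GEE cluster as site by phase, "so that every site corresponds to two clusters, one for every phase". That gives 24 clusters, 12 per regimen. Nothing in SAP sections 5, 8 or 9 provides a small-sample correction, an exact or score interval, or a rule for a phase without events.

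The expected 2MRGN BSI count is not stated. The protocol's rationale section says of a large German neonatal cohort that "the infection rates with Gram-negative pathogens and MRGN remained constant, i.a. 2.5-3%, and < 0.5%, respectively". The benchmarking section reports three 2MRGN sepsis cases among 319 very-low-birth-weight infants at one centre.

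**The concern.** In an identity-link model a risk of exactly zero lies on the boundary of the parameter space. If one regimen has no events, every cluster residual in it is zero, so the sandwich variance treats its risk as known without error. The reported interval then carries the uncertainty of the other regimen only. The software may also return no fit.

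2MRGN BSI is the infection closest to what the two regimens are meant to influence, so readers will look at this interval even though it is descriptive. An interval that just excludes zero on three events could be read as a signal of harm or benefit. If the command fails, a substitute would have to be chosen with the data in view.

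**Working it through.** **Inputs.**
- 12 sites and 2 phases (SAP section 5).
- About 150 screened infants per site and year: "GNN and PRIMAL centers treat on average 150 preterm and critically ill neonates per year with compulsory colonization screening" (protocol, sample size section). So N = 12 × 150 = 1,800 per regimen.
- ICC at most 0.01 (same section, given for the primary endpoint).
- 2MRGN BSI risk: not in the documents. The cohort ceiling of 0.5% times the share of 2MRGN among MRGN carriers at the single centre (30 of 47) gives 0.32%. A range of 0.1-0.3% is therefore an assumption. The single-centre 3/319 = 0.94% lies well above it, in a high-risk group.

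The plan computes no figure for this endpoint, so there is none to reproduce.

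**Planned interval.** For two groups with independence working correlation, each regimen contributes

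Var = Σ over clusters of (y_c − n_c·p)² / N²,

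and the interval is RD ± 1.96·SE. An empty regimen has y_c = 0 and p = 0, so it contributes 0.

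For 0 versus 3 events with equal clusters of 150, n_c·p = 3/12 = 0.25 and RD = 3/1,800 = 0.167 points. With the three events in three different site-phases, the sum is 3 × 0.75² + 9 × 0.25² = 2.25 and SE = 1.5/1,800 = 0.083 points.

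| Layout of the 3 events | Sum | SE (points) | z | 95% CI (points) |
|---|---|---|---|---|
| three site-phases | 2.25 | 0.083 | 2.00 | 0.003 to 0.330 |
| split 2 + 1 | 4.25 | 0.115 | 1.46 | −0.058 to 0.391 |
| all in one site-phase | 8.25 | 0.160 | 1.04 | −0.146 to 0.479 |

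The sign reverses if the intervention regimen is the empty one. Fisher's two-sided p for 0/1,800 versus 3/1,800 is 0.25.

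**Does the model fit?** `geepack` was not available, so the same binomial identity-link model was run with R `glm` on 288 month rows (24 clusters × 12 months).
- In 200 random layouts of 0 versus 3 events, 89 fits stopped with an error (45%) and 58 ended at the boundary or unconverged (29%).
- A separate run of 500 layouts per setting, for 0 versus 3 and 0 versus 4, gave 49-66% and 23-29%.
- With 1 versus 4, 2 versus 5 or 9 versus 9 events no fit failed. The failure is specific to an empty regimen.

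**How likely is an empty regimen?**
- ICC 0: P = 1 − (1 − e^(−1,800p))².
- ICC 0.01, beta-binomial, equal clusters: P0 = [B(a, b + 150)/B(a, b)]^12 with a = 99p and b = 99(1 − p), then P = 1 − (1 − P0)².
- The last column is from simulation with site sizes varying (CV 0.4); no such run was made for the last two rows.

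| Assumed risk | Expected events per regimen | ICC 0 | ICC 0.01, equal sizes | ICC 0.01, CV 0.4 |
|---|---|---|---|---|
| 0.1% | 1.8 | 30% | 56% | 57% |
| 0.2% | 3.6 | 5.4% | 21% | 22% |
| 0.3% | 5.4 | 0.9% | 7.2% | 8% |
| 0.5% | 9 | 0.02% | 0.8% | – |
| 0.94% | 16.9 | about 0 | 0.006% | – |

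**Alternative interval.** Newcombe's method combines the Wilson limits of each regimen. For 0/1,800 the Wilson limits are 0 and 3.84/1,803.84 = 0.213%; for 3/1,800 they are 0.057% and 0.489%. The lower limit is 0.167 − √[(0.167 − 0.057)² + 0.213²] = −0.073 points and the upper limit is 0.489 points. The empty regimen now contributes uncertainty, and zero is included.

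On admissions divided by the design effect, 1 + 149 × 0.01 = 2.49, the effective N is 1,800/2.49 = 723 and the interval is −0.378 to 0.827 points.

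**The case against.** A reader might infer that 0 versus 3 events would always be reported with an interval excluding zero. The table does not support that. Exclusion needs three different site-phases and is marginal even then. Shared site-phases are plausible for a transmissible organism. Given 0 versus 3, exclusion occurred in about 76% of simulations with independent events and equal clusters, about 51% with unequal clusters, and about 16% at 0.1% risk with ICC 0.01.

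A reader might also infer that the GEE interval is generally worse for rare events. Under no difference and ICC 0, it falsely excluded zero in 7.6% of simulated trials at 0.1% risk and 7.3% at 3%; at ICC 0.01 the figures were 2.1% and 7.2%. The excess over 5% reflects an uncorrected sandwich with 12 clusters per regimen, not rarity. With assumed risks of 0.2% versus 0.4-0.6%, the upper limit fell below the true difference in 5-9% of trials against a nominal 2.5%. That rests on assumed risks and is not part of this point.

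Three further objections stand. The event rate is assumed, and the single-centre 3 of 319 would make an empty regimen very unlikely if it held for all admissions. The ICC of 0.01 is a stated maximum for a 3% endpoint; at 0.1% risk it implies very strong clustering, so the upper ends of the ranges depend on it. The analysis is descriptive, so no formal conclusion turns on excluding zero.

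There is also a prior defect. SAP section 5 links 2MRGN BSI to `Anzahl_2MRGN_LOS`, but 9.4.2 attaches that label to the 2MRGN transmission variable, and `Anzahl_2MRGN_LOS` is not among the five modelled pairs. As written, the 2MRGN BSI count is not analysed. The endpoint is plainly intended, so the sparse-event gap remains once the labels are corrected.

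Finally, a score interval on the design-effect scale alone would be too blunt. For 0 versus 10 events it runs from −0.072 to 1.417 points and still includes zero although Fisher p = 0.002. The unclustered version gives 0.224 to 1.020. This is why both should be shown.

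**Conclusion.** The point holds in a limited form. When one regimen has no events, the method in SAP 9.4.2 either gives no interval or gives one that ignores that regimen's uncertainty, and the plan names no alternative. The chance of this for 2MRGN BSI runs from about 1% (risk 0.3%, ICC 0) to about 57% (risk 0.1%, ICC 0.01), and is about 1% or less from 0.5% upwards. These figures assume about 1,800 admissions per regimen and a 2MRGN BSI rate that the documents do not give. The fit failures were seen in R `glm`, not in `geepack`. The primary endpoint is not affected: at the assumed 3%, 54 events per regimen are expected. Importance is low, because the analysis is descriptive.

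**What to change.** First reconcile SAP section 5 with 9.4.2, so that 2MRGN BSI is analysed with `Anzahl_2MRGN_LOS` and each other label is matched to its own count.

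Then add to 9.4.2: if either phase has no events for a patient-level secondary endpoint, or the identity-link model does not converge, event counts by phase and site are reported with a Newcombe score interval for the risk difference in place of the Wald GEE interval. The score interval is shown twice: without clustering, and on admissions divided by 2.49 (the design effect at the plan's maximum ICC) as a conservative bound.

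The cost is a label correction, a short addition to the SAP and a closed-form calculation, with no new data. The downside is a wider interval, and the design-effect version is very conservative if clustering is weak. The analysis stays descriptive.
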